## Abstract

**Background:**

Glioblastoma is the most frequent and a particularly malignant primary brain tumor with no efficacy-proven standard therapy for recurrence. It has recently been discovered that excitatory synapses of the AMPA-receptor subtype form between non-malignant brain neurons and tumor cells. This neuron-tumor network connectivity contributed to glioma progression and could be efficiently targeted with the EMA/FDA approved antiepileptic AMPA receptor inhibitor perampanel in preclinical studies. The PerSurge trial was designed to test the clinical potential of perampanel to reduce tumor cell network connectivity and tumor growth with an extended window-of-opportunity concept.

**Methods:**

PerSurge is a phase IIa clinical and translational treatment study around surgical resection of progressive or recurrent glioblastoma. In this multicenter, 2-arm parallel-group, double-blind superiority trial, patients are 1:1 randomized to either receive placebo or perampanel (*n* = 66 in total). It consists of a treatment and observation period of 60 days per patient, starting 30 days before a planned surgical resection, which itself is not part of the study interventions. Only patients with an expected safe waiting interval are included, and a safety MRI is performed. Tumor cell network connectivity from resected tumor tissue on single cell transcriptome level as well as AI-based assessment of tumor growth dynamics in T2/FLAIR MRI scans before resection will be analyzed as the co-primary endpoints. Secondary endpoints will include further imaging parameters such as pre- and postsurgical contrast enhanced MRI scans, postsurgical T2/FLAIR MRI scans, quality of life, cognitive testing, overall and progression-free survival as well as frequency of epileptic seizures. Further translational research will focus on additional biological aspects of neuron-tumor connectivity.

**Discussion:**

This trial is set up to assess first indications of clinical efficacy and tolerability of perampanel in recurrent glioblastoma, a repurposed drug which inhibits neuron-glioma synapses and thereby glioblastoma growth in preclinical models. If perampanel proved to be successful in the clinical setting, it would provide the first evidence that interference with neuron-cancer interactions may indeed lead to a benefit for patients, which would lay the foundation for a larger confirmatory trial in the future.

**Trial registration:**

EU-CT number: 2023-503938-52-00 30.11.2023.

## Background

With 3000 new cases per year in Germany, glioblastoma is the most common and most aggressive primary brain tumor. Its treatment is limited to surgery, radiotherapy, and chemotherapy, with the option of adding tumor-treating fields [1]. Newer, targeted therapies have not proven effective for the general patient population [2]. Glioblastoma show strong mechanisms of resistance, and thus after primary treatment, recurrence is inevitable. Recurrence is currently measured with primarily imaging-based criteria according to the response assessment in Neuro-oncology criteria (RANO); those MRI measurements are however not highly accurate and standardised [3].

Upon the recurrence of glioblastoma, there are no further standard treatment options [4] and the prognosis is poor (mean progression-free survival (PFS) 1.5 to 4.2 months and overall survival (OS) 8.6 to 9.1 months) [5]. Depending on the location, tumor burden, functional status and preconditions, a re-resection of the tumor can be beneficial for patients with recurrent glioblastoma and is currently performed in about a third of patients with recurrent glioblastoma [6, 7]. Since treatment options are limited at the point of recurrence, inclusion into a study is recommended for glioblastoma patients by the Society for Neuro-Oncology (SNO) and European Association for Neuro-Oncology [4, 8]. To develop further trials for patients, new biological insights of glioblastoma need to be translated from bench to bedside.

In recent years, a new concept of glioblastoma building an anatomical and communicating network among tumor cells and between glioblastoma cells and non-malignant brain cells such as neurons has emerged [9–12]. The network integration between glioblastoma cells is mediated by cellular membrane protrusions termed tumor microtubes (TMs, [9]). Through TMs, the glioblastoma cell network facilitates the tumor’s resistance to all standard therapies with highly connected glioblastoma cells surviving treatment and building more TMs to interconnect glioblastoma cells even more densely as well as mediating self-repair while non-connected cells die under treatment [9, 13].

Glioblastoma consist of highly invasive and proliferating cells populating the entire brain and a densely interconnected tumor core [9, 12, 14–16]. Both the invasive and more solid parts were found to be stimulated by synaptic input of neurons on glioblastoma cells [10, 11, 16]. Neurons build bona-fide synapses with glioblastoma cells, where glioblastoma cells are the postsynaptic partner. They receive growth and invasion stimuli from presynaptic neurons by postsynaptic α-amino-3-hydroxy-5-methyl-4-isoxazolepropionic acid (AMPA) receptors, preferentially located on TMs of glioblastoma cells [10, 11]. The inhibition of AMPA receptor activity by genetic or pharmacological perturbation with perampanel was shown to reduce glioma cell proliferation and invasion in patient-derived xenograft mouse models [10, 11]. Furthermore, with the preferential location of neuron-glioma synapses on TMs, they drive their formation, elongation, and dynamics, which are essential for the brain colonization of glioblastoma cells. Hence, the inhibition of AMPA-receptors by perampanel also reduced TM formation [17].

Because it is currently not known if perampanel shows comparable effects through inhibition of the neuron-glioma synapses in the human disease and if it could reduce tumor proliferation and potentially whole brain dissemination, this trial was developed to test perampanel in human glioblastoma.

The non-competitive AMPA-receptor inhibitor perampanel is an EMA-/FDA-approved compound for add-on therapy in epilepsy [18] with blood-brain-barrier penetrance and advantageous pharmacokinetics such as a terminal half-life 105 h and an effective half-life 48 h when no enzyme-inducing antiepileptic drugs are co-administered [19, 20]. For this indication it shows good efficacy by reduction of seizure frequency [21–23] and the tolerability in patients was satisfactory.

Up to half of all glioblastoma patients suffer from brain tumor-related epilepsy (BTRE) [24], with significant negative impact on quality of life. Perampanel has also been investigated in the treatment of BTRE, where it led to significantly improved seizure control in observational studies with a good tolerability profile [25–27]. Even in lower doses of 2–4 mg perampanel/day, studies have shown high responder rates of > 75%, and even no further epileptic seizures under treatment up to 50% [25–29].

Perampanel’s inhibitory effects on AMPA receptors on glioblastoma resulting in reduced tumor invasion, proliferation, and resistance-mediating formation of TMs in preclinical models paired with data for good tolerability and clinical applicability in patients lead to the PerSurge trial. Current data support a potential dual anti-tumor and anti-epileptic activity of perampanel in patients. In this proof-of-principle trial, the novel concept of disconnecting neuron-tumor networks is translated into the clinical practice. If the PerSurge trial provides a positive result, perampanel would become a candidate for a new tumor-specific therapy principle in glioblastoma.

## Methods and design

### Trial design

The PerSurge trial includes patients with recurrent or progressive glioblastoma with the indication for re-resection. At this stage of the disease, no established, efficacy-proven standard of care therapy is available. Patients will be carefully selected for the possibility to safely perform surgery after thirty days of perampanel treatment vs. placebo with the addition of an intermediate MRI to verify safety of postponing the surgery for a brief period. This is the basis for this window of opportunity trial concept where perampanel or placebo is applied and imaging-based readouts but also molecular analyses from resected material can be performed. While the resection itself is not part of the trial, its indication and the feasibility of its short delay are necessary for the inclusion into the PerSurge trial. The investigation of the resected tissue primarily by single nucleus RNA-Sequencing is crucial for verification of on-target effectivity of perampanel at the molecular level with confirmation of the new therapeutic concept to reduce glioblastoma connectivity by measuring the connectivity score [30]. The placebo group is deemed crucial to avoid any bias in analysis of the primary and secondary endpoints and the associated translational research.

Further continuation of perampanel or placebo after the surgery for another 30 days (treatment cycle 2) will not interfere with other tumor-specific therapies that might be planned after re-resection for the trial participant since wound healing after surgery and planning of the subsequent treatment is usually taking 4–5 weeks [8, 31]. Thus, after the postsurgical 30-day treatment cycle when the trial medication is concluded, the patient is able to timely start the next tumor-specific treatment such as re-radiation or chemotherapy, if medically indicated.

### Objectives and endpoints

#### Primary objectives and endpoints

The primary aim of the study is to evaluate changes in neuron-tumor synaptic connectivity in glioblastoma tissue and changes of tumor growth rate after 30-day perampanel treatment before surgery in comparison to placebo control. This will be assessed on the level of gene expression pattern levels evaluating the connectivity score from single cell RNA sequencing of resected tumor tissue [30]. Additionally, the tumor growth rate, i.e. the absolute change in log-transformed tumor volume [cm³], will be determined in blinded independent review of AI-supported quantifications of T2/FLAIR MRI studies between baseline and a pre-surgical MRI at day 30 after randomization [32]. Either objective will be regarded sufficient to prove effectivity of the treatment.

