### Statistical considerations

The statistical analysis will be performed by KKS (Coordination Center for Clinical Trials) Heidelberg. For the evaluation of the co-primary endpoints, the connectivity score and MRIs will be assessed. The connectivity score is calculated by subtraction of up- and downregulated connectivity score genes using bioinformatic analyses. The second primary endpoint of tumor growth rate in MRI from day 0 to day 30 will be measured with AI-based evaluation of log-transformed changes in tumor volumes over time using a linear mixed effects model.

Based on earlier studies [10, 30], it was determined that analysis of 25 patients from each group will lead to a 90% power to detect a probability of 0.211 that an observation is reduced in the perampanel group compared to the placebo group. A Wilcoxon (Mann-Whitney) rank-sum test with a 0.025 two-sided significance level will be applied. A normal distribution and effect size of 1.125, and more precisely, a minimum difference in means of 0.9 and a common standard deviation of 0.8, was presumed for the calculation of the probability of 0.211.

Earlier studies have proven high accuracy of longitudinal assessments of tumor burden [32] and a mean glioblastoma growth rate of 54% (+/- 15%) in 30 days [37]. Thus, based on expert estimation, a reduction of the tumor growth rate of 36% (+/-15%) within 30 days would be regarded as clinically relevant. Assuming normally distributed values, with a power of > 94% the above-mentioned difference in tumor growth rate could be detected if the sample size is 25 patients per group, using the Wilcoxon (Mann-Whitney) rank-sum test with a 0.025 two-sided significance level.

Thus, for statistical analyses, the study will include *n* = 50 patients to be analyzed, which was extrapolated to mean a screening for eligibility for *n* = 100 patients and allocation of *n* = 66 in a 1:1 randomization in each arm (perampanel vs. placebo) after assuming consent on 65% of eligible patients. It was calculated that including 25% missing information for the primary outcomes (no surgery performed, e.g. due to death before V2, i.e. connectivity score missing), 66 patients should be allocated to achieve 50 out of them to be analyzable. The secondary and translational outcomes will be analyzed exploratively.

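### Either-or primary endpoints are labelled co-primary, carry no stated step-down rule, and may each alone prove effectivity (minor)

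*Protocol article*

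**What the plan says.** In the protocol article, the Methods paragraph of the abstract states that the connectivity score and the MRI growth measure "will be analyzed as the co-primary endpoints". Statistical considerations repeats the label: "For the evaluation of the co-primary endpoints, the connectivity score and MRIs will be assessed".

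The decision rule is under Primary objectives and endpoints: "Either objective will be regarded sufficient to prove effectivity of the treatment".

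Statistical considerations gives the levels. For the connectivity score: "A Wilcoxon (Mann-Whitney) rank-sum test with a 0.025 two-sided significance level will be applied". The growth endpoint is powered "using the Wilcoxon (Mann-Whitney) rank-sum test with a 0.025 two-sided significance level". The article states no overall alpha and no step-down rule, and it excludes none.

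On the strength of the conclusion, the Discussion paragraph of the abstract presents the trial as an early look at efficacy ahead of a larger confirmatory trial. Trial design describes the tissue analysis as a check, at molecular level, that the drug acts on its target.

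**The concern.** Three features do not fit together.

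- **Label.** *Co-primary* commonly means that both endpoints must succeed. The decision rule and the two 0.025 levels describe alternatives, where one success is enough. Someone reading only the abstract would take the trial to be stricter than it is.
- **Testing.** With an either-or rule and a total of 0.05, nothing requires the second endpoint to stay at 0.025 once the first has been rejected. Holm's step-down releases that alpha without weakening error control. This affects whether the trial can show both effects, which is its most informative result: the article's closing Discussion stresses relating the biological effect to the antitumour effect.
- **Claim.** One of the two sufficient endpoints is a gene-expression score. The rule does not require the growth endpoint even to point in the right direction, so a finding about target engagement would be reported as proof that the treatment works.

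**Working it through.** **Inputs from Statistical considerations.** 25 analysed per group; two-sided 0.025 per endpoint; score difference 0.9 with SD 0.8 ("a minimum difference in means of 0.9 and a common standard deviation of 0.8"), so d = 0.9/0.8 = 1.125; control growth "a mean glioblastoma growth rate of 54% (+/- 15%) in 30 days". The growth target is read as 36% growth on treatment and the ± figure as an SD, so d = (54 − 36)/15 = 1.2.

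**1. The plan's own figures.** Noether's formula is n per group = (z₁₋α/₂ + z₁₋β)² / [6(P − 0.5)²], with P = Φ(−d/√2).

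- Score: P = Φ(−1.125/√2) = 0.213 (stated 0.211). With z-values 2.241 and 1.282, n = 12.41/[6(0.289)²] = 24.8 at P = 0.211, and 25.1 at P = 0.213. Power at 25 per group is 90.3% and 89.8%. This agrees with "analysis of 25 patients from each group will lead to a 90% power to detect a probability of 0.211". Simulating the Wilcoxon test itself gives about 93.4%.
- Growth: P = Φ(−1.2/√2) = 0.198. Noether power is 92.7% and simulation gives about 96.0%, on either side of the stated figure of more than 94%.
- Randomised: 50/0.75 = 66.7, against 66 stated. This is immaterial.

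**2. Error rate of the split.** 0.025 + 0.025 = 0.05 at most; under independence 1 − 0.975² = 0.0494. The either-or rule is fully covered.

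**3. Holm.** Test the smaller p at 0.025; if it passes, test the other at 0.05.

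- Both nulls true: a false rejection needs the smaller p ≤ 0.025, which has probability at most 0.05 under any dependence.
- One null true: rejecting it needs its own p ≤ 0.05 at most.
- The first step is still 0.025, so 25 per group and 66 randomised stand.
- At least one rejection occurs if and only if the smaller p ≤ 0.025, under either procedure.

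**4. Size of the gain.** Simulation with 60,000 runs per setting, 25 per arm, Wilcoxon for both endpoints, d = 1.125 and 1.2. The article gives no correlation between endpoints, so 0, 0.3 and 0.6 are assumed. Entries are percentages, fixed 0.025 → Holm.

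| Correlation | Score | Growth | Both | At least one |
|---|---|---|---|---|
| 0 | 93.51 → 96.48 | 95.87 → 97.82 | 89.63 → 94.55 | 99.75 → 99.75 |
| 0.3 | 93.33 → 96.23 | 96.17 → 97.79 | 90.18 → 94.71 | 99.31 → 99.31 |
| 0.6 | 93.40 → 96.01 | 96.10 → 97.50 | 90.92 → 94.94 | 98.58 → 98.58 |

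With no effect on either endpoint, the family-wise error is 4.49%, 4.44% and 4.31% at the three correlations, the same for both procedures. With a true score effect and no growth effect, false rejection of the growth null rises from about 2.3% to 4.3–4.6% under Holm. That is the price of the gain, and it stays within 5%.

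**5. The claim rule.** Suppose the drug moves the score as planned and does nothing for growth. The plan's own power figure implies that the trial meets its rule for proven effectivity about 90% of the time; simulation of at least one rejection gives 93.6–94.0%. No error rate is breached. The conclusion is simply wider than the hypothesis that was rejected.

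**The case against.** A reader might infer that the fixed split wastes power for the trial as defined. The documents do not support that. Success is one endpoint or the other, and the last column of the table shows no difference. The Bonferroni split is a valid, conservative choice, and joint significance is not a stated criterion of success.

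A reader might also infer that the plan rules out Holm. It does not. Both 0.025 levels stand in sample-size paragraphs, and 0.025 is also the correct planning level for Holm's first step. The step-down may be fixed in the full protocol or SAP, which are not shown. This stands, so Holm is recommended here only if it is not already specified.

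Gains well above five points for showing both can be produced, for example 28–38% → 41–49% at d = 0.7 for both endpoints. That effect size is not in the protocol and is only an illustration.

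On the label, the decision rule is stated outright and the alpha split follows it, so an analyst is unlikely to apply a both-must-win rule by mistake. This too stands: the label is a wording point.

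On the claim, the article is more cautious elsewhere, both in the abstract and in Trial design. That caution shows what is intended, but it does not change the success rule. The rule is explicit and sets no limit on what a win on the score alone may be said to show.

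**Conclusion.** The point holds as a minor one. The error control and the sample size are sound.

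- **Claim rule.** This is the most substantive part: a win on the score alone would be declared proof of effectivity, against the article's own description of the trial as an early look at efficacy.
- **Holm.** A free improvement over the method as stated: about 4 to 5 points for showing both (about 90% to about 95%), about 3 points for the score and about 2 (1.4 to 2.0) for growth. It adds nothing for at least one success.
- **Label.** Misleading, but without effect on the analysis.

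The figures assume an overall alpha of 0.05 (implied, not stated), endpoint correlation between 0 and 0.6, normal data with the design effects, the growth target read as 36% growth on treatment, and a Wilcoxon test for both endpoints. Statistical considerations also mentions a linear mixed effects model for growth. Holm's validity does not depend on which test supplies the p-value, although the exact gains would shift.

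**What to change.** 1. Call the two endpoints *alternative primary endpoints* throughout, and state an overall two-sided alpha of 0.05.
2. Unless the full protocol or SAP already does so, specify Holm: the smaller p-value at 0.025 and, if it passes, the other at 0.05.
3. Replace the either-suffices claim with conclusions tied to the endpoint: score alone, target engagement; growth alone, an indication of antitumour activity; both, proof of concept.

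The cost is wording in the protocol and SAP. The 66 randomised patients, the 25 per group and the 5% family-wise error do not change. The changes should be made before unblinding, because a claim rule revised after the results are known would not be credible.

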#### Secondary objectives and endpoints

Secondary objectives to evaluate the efficacy of perampanel in recurrent glioblastoma are the assessments of the kinetics in contrast-enhancing (T1CE images) tumor volume by central AI-based MRI analyses at the pre-surgical and postsurgical time point (day 30 and 60 after randomization) and T2/FLAIR tumor volume by central AI-based MRI assessment at the postsurgical time point. Especially the pre-surgical and post-surgical log-transformed tumor volume [cm³] per the Blinded Independent Review Committee (BIRC) are of interest. The health-related quality of life (HRQoL) and symptoms will be monitored by the patient questionnaires EORTC QLQ-C30 and QLQ-BN20 [33] and cognitive function will be surveilled with the mini-mental state examination (MMSE) [34]. The absolute change from baseline at post-operative day 30 in the C30 summary score and in total MMSE score will be evaluated. Overall survival (OS, time from the date of randomization to the date of death due to any cause) and progression-free survival (PFS, time from randomization until progression according to RANO criteria or death) further pose as secondary objectives [34]. Finally, a clinical evaluation of epileptic seizure activity by documentation of seizures by the patient will be performed at trial visits and the total number of epileptic seizures between baseline and post-operative day 30 (day 60 after randomization) will be analyzed. Safety will be evaluated by observing adverse events (AE), serious AEs and Suspected Unexpected Serious Adverse Reactions (SUSARs) of the trial drug until three days after the end of treatment.

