#### Study duration and trial sites

The total duration of the recruitment for patients for this study is planned for 20 months (24 months first patient in– last patient out). It is planned to start in Q4/2023. Patients will be treated for 60 days with perampanel vs. placebo (two 30-day cycles) and followed-up after four weeks after the end of treatment for a safety visit. Further follow-up of OS and PFS will be examined every three months until death or last documented contact of the last randomized patient. At trial initiation, recruitment in 13 trial sites which are all large brain tumor centers in Germany is planned.

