
### Interventions (Fig. 1; Table 1)

**Fig. 1 Fig1:**
[figure not shown]
Clinical trial concept. Schematic overview of the trial. Created with BioRender.com

**Table 1 Tab1:** Overview of visits and interventions

Study period	Enrolment	Treatment period (60 ± 3 days)					Post-treatment follow-up	
	Screening/Baseline						Safety follow up	OS & PFS follow-up
Visit no.	1	2	3	4	5	6	7	FU
**Timeline/Timepoint**	**D0**	**D16** **(± 2)**	**0–3 days** **prior** **resection**	**D30** **(± 3)** **tumour resection**	**0–3** **days** **after resection**	**POD30** **(± 3)** **EOT visit**	**4 weeks** **after last dose** **(EOT visit)**	**Every** **3 months**
Mode of scheduled visit	Outpatient/inpatient	Outpatient/inpatient	Outpatient/inpatient	Inpatient	Outpatient/inpatient	Outpatient/inpatient	Outpatient/inpatient	Outpatient/ tel. visit
Written Informed Consent^a^	**X**							
In-/Exclusion Criteria	**X**							
Demographics, medical and surgical history/ preexisting conditions (evaluated in analogy to CTCAE)	**X**							
Randomisation*	**X**							
Vital signs^b^	**X**		**X**			**X**	**X**	
Physical and neurological examination	**X**	**X**	**X**		**X**	**X**	**X**	
Concomitant medications/procedures	**X**	**X**	**X**	**X**	**X**	**X**	**X**	**X** ^c^
Karnofsky Performance Status Scale	**X**	**X**	**X**		**X**	**X**	**X**	
Mini Mental State Examination	**X**					**X**		
HRQoL: Patient questionnaires EORTC QLQ-C30, QLQ-BN20	**X**					**X**		
Adverse Events		**X**	**X**	**X**	**X**	**X**	**X**	
Documentation of epileptic seizures	**X** ^d^	**X**	**X**		**X**	**X**	**X**	

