### Adverse events

Adverse events (AE) are defined as any untoward medical occurrence in a patient who the study medication is applied to and that is not necessarily caused by the investigational medicinal product. AEs will be documented and graded by CTCAE V 5.0 [36] throughout the trial. This includes clinically relevant or relevant worsening of baseline physical and neurological findings as well as vital signs, electrocardiographies, and laboratory results. AEs will be assessed for their seriousness, relationship with the intervention, outcome, and the need to take action (e.g. changes in dosing) by the investigator. Serious adverse events (SAEs) are defined as any untoward medical occurrence that results in death, is life-threatening, requires or prolongs hospitalization, leads to persisting significant disability, birth defect, or is otherwise medically relevant. SAEs have to be reported to the pharmacovigilance department in the coordination center for clinical trials in Heidelberg within 24 h of becoming known to the investigator. All AEs throughout the trial will be summarized and displayed.

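### The safety observation window has conflicting end points: three days after treatment in the objectives, the four-week safety visit in Table 1, and no stated limit in the adverse events section

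*Protocol article*

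**What the plan says.** Four places in the article bear on how long safety is observed.

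- **Secondary objectives and endpoints.** Safety is evaluated by observing AEs, SAEs and "Suspected Unexpected Serious Adverse Reactions (SUSARs) of the trial drug until three days after the end of treatment".
- **Study duration and trial sites.** Patients are "followed-up after four weeks after the end of treatment for a safety visit".
- **Interventions, Table 1.** The row "Adverse Events" is blank at visit 1, marked at visits 2 to 7 and blank in long-term follow-up. Visit 7 is the safety follow-up, four weeks after the final dose. No footnote limits what the visit 7 mark covers.
- **Adverse events.** "AEs will be documented and graded by CTCAE V 5.0 [36] throughout the trial", and the section closes with "All AEs throughout the trial will be summarized and displayed". Neither sentence gives an end point, and the 24-hour SAE reporting duty has none either.

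The Background gives perampanel "terminal half-life 105 h and an effective half-life 48 h when no enzyme-inducing antiepileptic drugs are co-administered". Enzyme-inducing antiepileptics are an exclusion criterion, so these half-lives are the relevant ones here.

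**The concern.** An event that starts ten days after the final dose lies outside the safety evaluation on the wording of the objectives. The same event is due for recording under Table 1 and for display under the adverse events section. This is a conflict between statements in the text as it stands, not a detail that the article has left to a longer document.

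At stake is which AEs and SAEs count in the comparison of the arms. The Abstract names tolerability among the things the trial is meant to assess, and the drug is eliminated slowly. A short window closes while patients in the perampanel arm are still exposed. If the window is not fixed, the choice could also be made after the data are known.

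**Working it through.** No sample size, power or alpha figure is involved, and the plan gives no figure of its own to reproduce. The check compares the windows and then uses the article's half-lives.

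**1. Length of the gap**
- Objectives section: 3 days after treatment.
- Table 1, visit 7: 4 weeks = 28 days after the final dose.
- Difference: 28 − 3 = 25 days, or 25/28 = 89% of the period up to visit 7.
- Adverse events section: no end point. Read literally, it would run past visit 7 into long-term follow-up, where the AE row is blank.

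**2. What is scheduled inside the gap**
- Table 1 and the blood sampling section place haematology and clinical chemistry at baseline, shortly before resection, within three days after resection, and at the safety follow-up. None is scheduled at visit 6, the end-of-treatment visit.
- The adverse events section counts clinically relevant worsening of laboratory results as an AE.
- Under the three-day limit, therefore, no scheduled haematology or chemistry result after the early postoperative sample enters the safety evaluation. That leaves nearly all of the second 30-day cycle without one.
- Physical and neurological examination and vital signs are less affected: both are done at visit 6 as well as visit 7.

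**3. Drug remaining when each window closes**

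Assuming first-order elimination, the fraction remaining is 0.5^(hours ÷ half-life).

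| Time after final dose | Half-life used | Half-lives elapsed | Level remaining |
|---|---|---|---|
| 3 days = 72 h | 105 h (terminal) | 72/105 = 0.69 | 62% |
| 3 days = 72 h | 48 h (effective) | 72/48 = 1.5 | 35% |
| 28 days = 672 h | 105 h (terminal) | 672/105 = 6.4 | 1.2% |
| 28 days = 672 h | 48 h (effective) | 672/48 = 14 | under 0.01% |

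Three days is less than one terminal half-life but one and a half effective half-lives. On either figure about a third or more of the level remains at three days, and about 1% or less at visit 7.

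**The case against.** The strongest reply is that the statements serve different purposes. The three-day limit stands under secondary objectives and could define a comparative safety endpoint, while Table 1 schedules collection. A short endpoint window inside a longer collection period is coherent. The visit 7 mark could also mean only that earlier events are followed to resolution. Either reading is possible, but the article states neither, and its promise to display all AEs fits neither well. The full protocol may settle the point.

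There is also a plausible reason for a short window. The trial design section lets the next tumour therapy start once trial medication ends, so events in the following weeks may reflect re-radiation or chemotherapy. With about 33 patients per arm (66/2), that could blur the comparison. This objection stands, and it is why late events need separate display.

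A reader might infer more than the documents support:

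- *That late events will be left out of the safety tables.* The adverse events section says that all AEs are summarized. They drop out only if the objectives section overrides it, and nothing says so.
- *That sites will apply different windows.* The article does not say that sites work from it, and Table 1 schedules AE recording at visit 7 for every patient.
- *That seizures after stopping the drug will be missed.* Seizure documentation has its own row in Table 1, marked at visit 7, although the seizure-count endpoint ends at postoperative day 30.
- *That every event up to four weeks is treatment-emergent.* The possible start of the next therapy argues against that label.
- *That the half-life proves the three-day window wrong.* The argument is weaker on the 48 h figure, and the contradiction does not depend on it.

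**Conclusion.** The contradiction is real and lies in the current text: three days, about 28 days, and no stated limit. If the three-day limit governs, 25 of the 28 days up to visit 7 are excluded, together with the only scheduled haematology and chemistry after the early postoperative sample, while about 35% to 62% of the drug level remains. If it does not govern, the loss does not arise and the sentence in the objectives section is simply wrong or incomplete. The documents do not show which is intended.

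The percentages assume first-order elimination, the half-lives quoted in the Background, and that treatment ends with the final dose. The 25-day gap needs only the last of these.

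This concerns a secondary safety outcome. Neither co-primary endpoint is touched, and any single window would apply equally to both blinded arms. It should be corrected but is not a must-fix.

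**What to change.** Reconcile the secondary objectives section, Table 1 and the adverse events section by stating one window for each of three things: AE onset, SAE reporting and the safety tables. If visit 7 is meant only to follow up earlier events, say so in a footnote to Table 1.

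For the tables, use what is already scheduled. Tabulate AEs and SAEs to visit 7 by arm, in two parts: events up to three days after the final dose, and events from then to visit 7. Flag events that start after the next tumour therapy has begun. This preserves the short-window comparison and keeps the later data visible without calling all of it treatment-emergent.

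The cost is a few sentences in the protocol and analysis plan plus one extra column. The visit, its AE entry and its laboratory tests already exist, and Table 1 already records concomitant medications and procedures at visit 7, which should supply the date for the flag. The small downside is that some late events will reflect the next therapy and not the trial drug.
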